## Abstract

Borderline personality disorder (BPD) represents a severe mental condition that is usually characterized by distressing identity disturbances. Although most prevailing explanatory models and psychotherapy approaches consider and intervene on self-concept, they seem not to recognize or explore idiosyncratic cognitive conflicts that patients may experience. These conflicts, which have been conceptualized as “implicative dilemmas” and “dilemmatic constructs” by personal construct theorists, could be considered as key elements of the explanatory model for BPD to provide a better understanding of this disorder and possibly enhance the effectiveness of contemporary psychotherapeutic approaches. The current study (Identifier: NCT04498104) aims to examine the characteristics of the interpersonal cognitive system of a group of patients diagnosed with BPD, using the repertory grid technique, and to compare them with those of a community sample. We will test if BPD participants are more affected by cognitive conflicts than controls. Additionally, we will gauge the association between cognitive conflicts and symptom severity as well as their predictive capacity of treatment outcome. The obtained results will be a necessary step to determine if cognitive conflicts have a substantial role on the explanation of BPD. It could also help to consider the development of a conflict resolution intervention module for this disorder.

## 1. Introduction

Borderline personality disorder (BPD) is a highly disabling condition that has a severe impact on quality of life and psychosocial functioning of those affected [1]. Its prevalence is estimated in 1–2% of the general population, although this rate can go up to 22% in clinical settings [2].

People with BPD may experience a broad variety of clinical manifestations but most of them are related to emotional, interpersonal and self-image instability, along with extreme and impulsive reasoning and demeanor. It is generally understood that mood, sense of identity and relationships tend to drastically fluctuate depending on different factors, causing psychological distress that is intended to be alleviated by responding to the emerging urges with little or no reflection on the consequences [3]. According to the fifth edition of the Diagnostic and Statistical Manual of Mental Disorders (DSM-5) [4], an individual should meet five out of the nine possible criteria to receive a BPD diagnosis. Therefore, it is usually said that two patients with a diagnosis of BPD might have quite different experiences due to the wide diversity of possible symptom combinations they can undergo. On the other hand, the prototypical patient does not always tend to seek assistance to mitigate BPD symptoms, but rather to find relief from comorbid syndromes such as depression, anxiety or eating disorders, among others [5]. This lack of syndromic unity has prompted the creation of dimensional models of personality disorders. As a new feature, this latest version of the DSM includes in its third section a categorical-dimensional hybrid proposal that understands all personality disorders as a single entity composed of five broad domains and 25 specific traits instead of several qualitatively different mental conditions [4].

It is common for individuals with a BPD diagnosis to engage in suicidal and parasuicidal ideation or behavior and substance abuse as a consequence of their main symptoms [3]. It has been generally reported that up to 90% of BPD patients develop a pattern of nonsuicidal self-injuries (NSSIs), such as cutting or burning [6], and about 60–70% commit at least one unsuccessful suicide attempt [7], although other studies find even greater prevalence rates (e.g., [8]). It is estimated that approximately 10% of people with BPD lose their life to suicide [9], increasing by 50 times the suicide probability compared to non-clinical population, which makes BPD one of the major life-threatening mental illnesses [10]. Thus, the need to find effective therapeutic strategies that can diminish these rates deserves critical attention from researchers, clinicians and health authorities.

Studies of up-to-date therapeutic resources for BPD show that pharmacological treatment is only indicated in certain cases, mainly when directly proposed to address certain features of the whole clinical picture [11]. Therefore, psychotherapy is one of the main resources for mental health practitioners when treating these patients [12]. Currently, there are several psychological treatments and explanatory models designed or adapted for people diagnosed with BPD but not all of them have been equally supported by empirical evidence. Although none of the existing proposals has proven to be clearly superior to the others, dialectical behavior therapy (DBT) [13,14,15] and mentalization-based treatment (MBT) [16,17] seem to stand out in their therapeutic effectiveness thanks to the favorable data reported in multiple studies [18]. These approaches come from different psychological models that focus on different aspects when explaining BPD, the former from a cognitive-behavioral base and the latter from a psychodynamic approach. Nonetheless, they also integrate elements and resources from other different psychological orientations and currents of thought. Although they have been reported to be useful in many cases, after detailed analysis, these therapies tend to be successful mainly for certain symptomatic domains [18], leaving a remarkable need to focus on other unattended clinical necessities of people with BPD [19]. Perhaps the explanatory models from which these psychotherapies emerge might have underestimated important aspects, such as the level of conflict in the cognitive system of these patients.

To advance in the understanding of BPD and further improve these psychotherapies or any other therapeutic strategies, perhaps it could be useful to complement them with contributions from a constructivist base. Cognitive conflict [20] is one of the concepts that could be enriching from this perspective. The essence behind this term is the simultaneous presence of two or more cognitive contents (thoughts, beliefs, values, etc.) that are opposed or contradictory and therefore may create internal tension that result in various forms of psychological distress. It is based on personal construct theory (PCT) [21] and it might explain the lack of psychological stability, which is characteristic of people with BPD. Considering that personal identity, interpersonal relationships and affectivity are very unstable domains for these people, we could expect to find high levels of inner conflict that might hinder balance in these areas due to the presence of personal dilemmas related to the construction of the self and others. If that is the case, this issue should be addressed by mental health professionals. Though some psychotherapeutic approaches may deal with some sorts of cognitive conflicts, their content and structure are usually formulated with constructs derived from the theories on which they are based rather than coming from the personal terms and experience of each patient. In the treatment of BPD, it is not usual to perform a systematic assessment of cognitive conflicts and their role in the actual clinical manifestation of the disorder. However, dilemma-focused therapy, a constructivist therapy based psychological intervention, undertakes a systematic exploration of the patient’s cognitive system to search for idiosyncratic dilemmas. Results of this careful assessment are used to formulate a precise clinical hypothesis and treatment plans for each patient. As BPD is a heterogeneous condition with multiple possible diagnostic criteria combinations, adapting to each patient and exploring their construction system and personal cognitive conflicts would be more beneficial than to attribute general, potentially erratic or general assumptions derived from a given academic or theoretical bias [22]. Idiosyncratic inner conflict is a very unexplored field that could potentially be important in the treatment of BPD.

The repertory grid technique (RGT) is a complex assessment instrument created in the context of PCT and used to evaluate the individual’s personal constructs (bipolar dimensions of subjective meaning) and their belief system in order to have access to their sense of identity and interpersonal perception [23,24]. Using this instrument, it is possible to measure cognitive conflicts in the form of implicative dilemmas (not performing a desired change due to fear of changing one’s desired identity aspects) and dilemmatic constructs (not knowing how oneself wants to ideally be), among other cognitive indicators [25]. This tool could be useful to explore the world of personal meanings of patients with BPD in order to facilitate the detection of the cognitive conflicts they may experience as has been done in other clinical populations [26]. Adding a dilemma-focused intervention [27,28] to the existing treatments for BPD could optimize the psychological treatment for this type of patient, as has been already done with depression [29].

## 2. Objectives and Hypothesis

The central aim of this research is to assess cognitive conflicts in individuals with a diagnosis of BPD to determine their role in the explanatory model of this disorder. These findings would permit the consideration of adapting a dilemma-focused intervention module for these patients. In addition, it would be interesting to explore other characteristics of the construction of self and others that are assessed with the RGT. The specific objectives of this study are:To verify the hypothesis that patients with BPD present more cognitive conflicts (i.e., implicative dilemmas and dilemmatic constructs) than a sample from the general population.To explore the content of cognitive conflicts in patients with BPD.To examine if the presence and number of cognitive conflicts are associated with severity of emotional symptoms in BPD patients.To test whether the presence and number of cognitive conflicts has any capacity to predict treatment outcome (in terms of psychological distress and BPD symptomatology).To explore the relevance of other aspects of the construction of self and others to explain the psychological functioning of patients with a BPD diagnosis.

It is expected that:The percentage of participants with implicative dilemmas and/or dilemmatic constructs will be superior in the group of patients diagnosed with BPD compared to a control group (community sample).The number of implicative dilemmas and/or dilemmatic constructs will be higher in the BPD group than in the control group.The presence and higher number of cognitive conflicts will be associated with greater levels of general distress clinical symptomatology (such as depression, anxiety, etc.).The presence and higher number of cognitive conflicts will predict poor treatment outcome one year after the initial assessment.

For exploratory purposes, we will also study the content of implicative dilemmas and dilemmatic constructs, and the differences with the control group regarding self-construction measures (self-ideal discrepancy, self-others discrepancy, ideal-others discrepancy) and other characteristics of the construction system (differentiation and polarization) and its association with other clinical and sociodemographic measures.

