#### 3.2.4. Repertory Grid Technique (RGT)

The repertory grid technique is a personalized procedure using a structured interview designed to make explicit personal constructs that interviewees use to interpret and organize their interpersonal world [23,24]. It begins by identifying significant family and friends (here termed elements) and then the patient is asked to compare them (including “self now” and “ideal self”) in pairs in order to elicit the constructs used to differentiate among these elements. Once the interviewee offers a verbal tag to describe an element (e.g., “active”), they are asked to utter the opposed meaning (e.g., “passive”) to complete the bipolar dimension represented by the personal construct. Finally, the patient is asked to rate each relevant person of their interpersonal world (in addition to their actual and ideal selves) according to each personal construct expressed using a seven-point Likert scale. This creates a data matrix of elements with constructs which can be analyzed to extract several cognitive indices.

As previously mentioned, one of the main measures the RGT can provide is cognitive conflict, through the identification of implicative dilemmas and dilemmatic constructs. In order to detect the presence of implicative dilemmas, first we need to identify both congruent and discrepant constructs. The former ones are defined by the congruence between the scores of the “self now” and “ideal self” elements in that construct (e.g., being a “protector” in the example of Feixas et al. [36]), and the latter by a dissonance (or dissimilarity) between these two elements, indicating a discrepancy in the way individuals perceive themselves and how they would desire to be (e.g., not “loving herself” but wishing to do it, in the same case example). An implicative dilemma is detected when a correlation between the scores of a congruent construct and a discrepant construct is found, when the direction that the desired change indicated by the discrepant construct is associated with the loss of congruence for the self (e.g., “loving herself” is associated with being “unemotional”, the opposite pole of being a “protector”). Therefore, discrepant constructs per se do not define a conflict or dilemma but are just a discrepancy (see other measures below), a target for change. 

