○Self-ideal discrepancy: Higher distances between “self now” and “ideal self” are usually interpreted as low self-esteem.○Self-others discrepancy: While high scores indicate perceived social isolation, low scores point out a high level of identification with others.○Ideal-others discrepancy: Conceived to measure perceived adequacy of significant others, large distances indicate a critical view of others.Interpersonal dichotomous thinking: Computing the total amount of extreme scores (“1” and “7”) yields the polarization index. This measure reveals if there is a tendency towards dichotomous thinking (all or nothing) when construing self and others.Interpersonal cognitive differentiation: This domain is measured through the percentage of variance accounted for the first factor (PVAFF), an index that results from the correspondence analysis of the whole grid data matrix. A large size of the first factor indicates a tendency to interpret interpersonal experiences in a unidimensional way, while a low PVAFF allows for a more differentiated view, with more nuances, suggesting that multiple points of view are available when construing self and others.

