### 3.4. Data Analysis

All data collected with the RGT will be analyzed with the program GRIDCOR 6.0 (Universitat de Barcelona, Barcelona, Spain), [43] to obtain relevant cognitive indexes, including cognitive conflict indicators. All measures derived from the RGT along with the rest of the quantitative information obtained by the rest of the instruments will be introduced and statistically analyzed with SPSS v.26 (IBM, Armnok, USA).

In order to prove the first two hypotheses, chi-square tests and variance analyses will be performed to determine whether there exist differences between groups regarding the presence, number and intensity of cognitive conflicts and, secondarily, other measures derived from the RGT. According to the obtained results, a logistic regression will be conducted to determine the capacity of the studied variables to predict group allocation. In the previous tests, and depending on the variations found between samples, relevant sociodemographic and clinical variables will be statistically controlled.

Considering only the clinical sample, correlations and analysis of variance will be performed to study the relations between cognitive variables (i.e., number and intensity of cognitive conflicts) and the clinical variables such as those retrieved from CORE-OM, DASS-21 and DIB-R scales and SCID-II BPD diagnostic criteria type and amount. Linear regression may be conducted depending on these results to assess the capacity of the studied cognitive conflict variables to predict progress one year later. In addition, based on the variability found in the sample, other variables will be statistically controlled. The study of predictive capacity of the variables with respect to treatment outcome one year later will be approached using regressions.

For the content analysis, two investigators will encode the personal constructs obtained with the RGT following the CSPC in the BPD sample. Differences in the content between congruent and discrepant constructs will be explored using chi-square tests.

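### Conflict counts and polarization are compared between groups as raw totals, with no stated control for grid size, so any group difference in grid size would confound them

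*Protocol article*

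**What the plan says.** All references are to the protocol article.

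- **Outcomes (section 2).** Hypothesis 1 concerns presence: "The percentage of participants with implicative dilemmas and/or dilemmatic constructs will be superior in the group of patients diagnosed with BPD", compared with the control group. Hypothesis 2 concerns number: "The number of implicative dilemmas and/or dilemmatic constructs will be higher in the BPD group than in the control group". No denominator is attached to either.
- **Grid (section 3.2.4).** The text calls the technique personalized: "The repertory grid technique is a personalized procedure using a structured interview designed to make explicit personal constructs". On the elements: "It begins by identifying significant family and friends (here termed elements". These are then compared "in pairs in order to elicit the constructs used to differentiate among these elements". The article gives no number for elements or constructs.
- **Units of conflict (section 3.2.4).** On implicative dilemmas: "An implicative dilemma is detected when a correlation between the scores of a congruent construct and a discrepant construct is found". The unit is therefore a pair of constructs. A dilemmatic construct is a single construct on which the ideal self is rated at the midpoint.
- **Polarization (section 3.2.4).** It is obtained by "Computing the total amount of extreme scores", that is, ratings of 1 and 7. The differentiation index in the same list is a percentage.
- **Analysis (section 3.4).** Chi-square tests and analyses of variance examine "differences between groups regarding the presence, number and intensity of cognitive conflicts". The covariates foreseen for the group comparison are sociodemographic and clinical.
- **Controls (section 3.1.1).** They come from a student sample and a community sample recruited in 2012 to 2015, matched on age, gender and educational level.

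**The concern.** Each measure is a count whose expected value depends on how large the grid is as well as on how conflicted the person is. A grid with more constructs offers more chances of a midpoint rating, and still more chances of a conflicting pair. A grid with more cells offers more chances of an extreme rating.

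That would matter little if all grids were the same size, or if both groups had been interviewed together under one rule. The article states neither. The patients' grids are new and the controls' grids come from earlier studies, and matching on age, gender and education does not equalise the number of constructs elicited.

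Hypotheses 1 and 2 are at stake. If BPD grids are larger on average, both could be supported with no difference in conflict density. If they are smaller, a real difference could be hidden.

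**Working it through.** **Inputs from the article.** 78 per group, two-sided 5% test (section 3.1), and the units of conflict listed above. The article reports no grid size or conflict rate, so there is no figure of its own to reproduce on this point. Everything else below is an assumption.

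**Step 1: how opportunity scales with grid size.** Take k constructs and e elements, with conflict density held equal.

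- Dilemmatic constructs scale with k.
- Implicative dilemmas scale with construct pairs, k(k − 1)/2.
- Extreme ratings scale with k × e.

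Number of construct pairs:

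| Constructs | Pairs | Ratio to 15 |
|---|---|---|
| 15 | 15 × 14 / 2 = 105 | 1.00 |
| 16.5 | 16.5 × 15.5 / 2 = 127.9 | 1.22 |
| 18 | 18 × 17 / 2 = 153 | 1.46 |

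So 20% more constructs (18 against 15) gives 46% more pairs.

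**Step 2: effect on the test of number.** Two simulations were run in which the groups had the same conflict density and differed only in grid size, with 78 per group and t-tests (equivalent to analysis of variance for two groups).

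- *Model A* (4,000 replicates): constructs Poisson around the group mean; implicative dilemmas gamma-Poisson at 0.03 per pair, shape 0.5 or 1.
- *Model B* (3,000 replicates): constructs with SD 3; 14 elements (SD 2) in each group unless stated; 10% of constructs dilemmatic; 25% discrepant; 5% of eligible pairs in dilemma; 25% of ratings extreme; between-person intraclass correlation (ICC) 0.10 or 0.03.

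Rejection rate of the 5% test:

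| Mean constructs | Measure | Raw total, A | Raw total, B |
|---|---|---|---|
| 15 v 15 | implicative dilemmas | about 5% | 4% |
| 16.5 v 15 | implicative dilemmas | 10% to 14% | not run |
| 18 v 15 | implicative dilemmas | 24% to 39% | 18% to 37% |
| 18 v 15 | dilemmatic constructs | not run | 15% to 23% |
| 18 v 15 | polarization | not run | 45% to 79% |

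Dividing by pairs, constructs or ratings gave rejection rates between 4.0% and 6.2% throughout. This is largely built in, because the data were generated at constant density. What the comparison shows is that grid size alone drives the excess.

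A difference in elements only (16 v 14) left dilemmatic and implicative counts at about 5% but raised polarization to 26%. Any effect of the number of elements on the correlations that define dilemmas was not modelled.

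**Step 3: effect on presence.** Percentage of people with at least one implicative dilemma, 15 then 18 constructs:

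- Model A, shape 0.5: 61% to 67%.
- Model A, shape 1: 73% to 80%.
- Model B, ICC 0.10: 36.5% to 43.1%, a gap of 6.6 points.
- Model B, ICC 0.03: 51.1% to 61.3%, a gap of 10.2 points.

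The gap is thus about 6 to 7 points in three of the four settings and larger when people vary little in conflict density.

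**The case against.** The strongest reply is that the article never says grid size is free. It describes a structured interview, leaves the indices to the GRIDCOR program, and is a condensed account. If the full procedure fixes the number of elements and constructs, the bias disappears. It is also fair that hypothesis 2 names the number of conflicts as its target, that the separate intensity measure (not defined in the article) may already be relative to grid size, and that polarization is exploratory.

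Most of this limits the point without removing it. A reader might infer that interviewees set their own grid size, or that the two groups' grids do differ. The text supports neither as fact: it describes individual elicitation and states no rule. The concern is therefore conditional. The choice of raw number and total as the compared measures, however, is stated, and number and presence are tested in their own right whatever intensity turns out to be.

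Three further readings go too far:

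- *That the correlations with symptoms inside the BPD sample are biased in the same way.* Grid size distorts them only if it is related to symptoms. Otherwise it mainly adds noise. Section 3.4 also leaves room there to control other variables.
- *That presence would differ by 13 points.* Treating pairs as independent at 0.5% each gives 1 − 0.995^105 = 41% against 1 − 0.995^153 = 54%. That ignores variation between people; the models that allow for it mostly give about half the gap.
- *That all pairs are the only correct denominator.* A dilemma needs one congruent and one discrepant construct, so congruent × discrepant pairs are also defensible. Dividing by all pairs does not correct for a different congruent/discrepant split.

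**Conclusion.** The point holds in conditional form. The plan fixes raw number, presence and a raw total as the compared measures, takes controls from other studies, and names no control for grid size in the group comparison. If mean grid size differs between groups, hypotheses 1 and 2 and the polarization comparison are confounded with it, in a direction that the article does not let us determine.

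The illustration rests on an assumed gap of 18 versus 15 constructs, with equal conflict density and 78 per group: roughly 18% to 39% false positives for raw implicative-dilemma counts in place of 5%. A gap of 1.5 constructs gives 10% to 14%, and no gap gives about 5%. The serious part is the number and presence of conflicts. The change should be made before the groups are compared.

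**What to change.** For the comparison of BPD patients with controls:

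- analyse implicative dilemmas as a percentage of construct pairs, or with a negative binomial model with log(pairs) as offset;
- analyse dilemmatic constructs as a percentage of constructs;
- analyse polarization as a percentage of all ratings in the grid;
- adjust the presence comparison for the number of constructs, for example by logistic regression;
- report the number of constructs and elements by group;
- keep raw counts as descriptive results.

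A sensitivity analysis may use congruent × discrepant pairs as the denominator for implicative dilemmas. If the full procedure does fix the grid dimensions in both the new and the earlier studies, saying so in one sentence would settle the matter.

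The cost is one division or offset per measure, using dimensions already held in every grid, with no new data collection. The small downside is that the raw count is no longer the headline figure, so hypothesis 2 needs rewording to match.
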